## Abstract

**Background:**

Supraclavicular nodal (SCL) irradiation is commonly used for patients with high-risk breast cancer after breast surgery. The Radiation Therapy Oncology Group (RTOG) and European Society for Radiotherapy and Oncology (ESTRO) breast contouring atlases delineate the medial part of the SCL region, while excluding the posterolateral part. However, recent studies have found that a substantial proportion of SCL failures are located in the posterolateral SCL region, outside of the RTOG/ESTRO-defined SCL target volumes. Consequently, many radiation oncologists advocate for enlarging the SCL irradiation target volume to include both the medial and posterolateral SCL regions. Nevertheless, it remains uncertain whether adding the posterolateral SCL irradiation improves survival outcomes for high-risk breast cancer patients.

**Methods:**

The SUCLANODE trial is an open-label, multicenter, randomized, phase 3 trial comparing the efficacy and adverse events of medial SCL irradiation (M-SCLI group) and medial plus posterolateral SCL irradiation (entire SCL irradiation, E-SCLI group) in high-risk breast cancer patients who underwent breast conserving-surgery or mastectomy. Patients with pathological N2-3b disease following initial surgery, or clinical stage III or pathological N1-3b if receiving neoadjuvant systemic therapy, are eligible and randomly assigned (1:1) to M-SCLI group and E-SCLI group. Stratification is by chemotherapy sequence (neoadjuvant vs. adjuvant), T stage (T3-4 vs. T1-2), N stage (N1-2 vs. N3), and ER status (positive vs. negative). Other radiation volumes are identical in the two arms, including breast/chest wall, undissected axillary lymph node, and internal mammary node. Advanced intensity modulated radiation therapy (IMRT), volumetric modulated arc therapy (VMAT), or tomotherapy techniques are recommended. Both hypofractionated and conventional fractionation schedules are permitted. The primary end point is invasive disease-free survival, and secondary end points included overall survival, SCL recurrence, local-regional recurrence, distance recurrence, safety outcome, and patient-reported outcomes. The target sample size is 1650 participants.

**Discussion:**

The results of the SUCLANODE trial will provide high-level evidence regarding whether adding posterolateral SCL irradiation to medial SCL target volume provides survival benefit in patients with high-risk breast cancer.

**Trial registration:**

ClinicalTrials.gov Identifier: NCT05059379. Registered 28 September 2021, https://www.clinicaltrials.gov/ct2/show/NCT05059379.

## Background

Numerous randomized clinical trials and meta-analyses have demonstrated that radiotherapy significantly reduces local-regional recurrence and improves disease-free survival and breast cancer-specific survival in high-risk breast cancer patients after primary breast surgery [1–4]. Additionally, patients with pathologically positive lymph node after neoadjuvant chemotherapy and surgery have been shown to have high risk of recurrence and could benefit from postoperative radiotherapy [5]. Based on these evidences, it is recommended that patients with pathologically stage III disease after primary breast surgery, as well as those with pathologically positive lymph nodes following neoadjuvant systemic therapy and breast surgery, should receive postoperative breast/chest wall and regional nodal irradiation (RNI).

The supraclavicular nodal (SCL) region is the most frequent site of regional nodal failure after mastectomy and breast-conserving surgery, thus remained an essential component of RNI [6]. In the era of traditional 2-dimensional (2D) radiotherapy, the SCL field was defined based on anatomical boundaries. Typically, the lateral border was located lateral to humeral head with a block to shield the humeral head or medial 2/3 clavicle. Typical radiation dose coverage includes only medial part of SCL region, not extending to the posterolateral SCL fossa [3, 4]. In the modern radiotherapy era, with the advent of computed-tomography (CT)-based radiation treatment planning, atlas consensus was proposed by the Radiation Therapy Oncology Group (RTOG) in 2009 and the European Society for Radiotherapy and Oncology (ESTRO) in 2015 [7, 8]. The RTOG define the dosal and lateral boundaries of the SCL clinical target volume (CTV) at the anterior aspect of the scalene muscle and lateral edge of sternocleidomastoid muscle (cranial) and the junction of the 1st rib and clavicle (caudal), respectively [7]. The ESTRO define the dosal and lateral boundaries of the SCL CTV at pleura and including the anterior scalene muscles and connecting to the medial border of axillary level 3, respectively [8]. Therefore, both RTOG and ESTRO consensus still encompass only the medial part of SCL region.

However, several recent studies have focused on mapping the locations of the SCL metastases and have demonstrated a notable SCL metastases occurred in the overlooked posterolateral part of SCL region (14 ~ 82%), thus outside of the RTOG and ESTRO-defined SCL CTVs [9–13]. Consequently, a growing number of radiation oncologists advocate for enlarging SCL CTV to include both medial and posterolateral SCL region, creating what is referred to as the “entire SCL region”. In the context of ongoing clinical trials, the RADCOMP atlas for RTOG 3509/3510 trial has introduced the posterolateral SCL as an optional volume to consider for irradiation [14]. Additionally, a phase 3 randomized clinical trial exploring the impact of internal mammary nodal irradiation on disease-free survival in high-risk breast cancer patients in currently recruited in China, with the SCL CTV encompassing the entire SCL region [15]. However, some other clinical trials, such as NRG 9353, Alliance A11022, Danish Breast Cancer Cooperative Group (DBCG) RT Recon Trial, and DBCG HYPO II Trial still define the SCL CTV based on RTOG atlas or ESTRO guidelines. Therefore, controversy exists in practice regarding the optimal definition of the SCL target volume. Recently, TransAtlantic Radiation Oncology Network conducted a review and recommended that SCL CTV should follow the RTOG or the RADCOMP atlas for patients at high and very high regional recurrence risk [16].

We previously conducted a retrospective study comparing cancer outcomes and toxicities between medial SCL irradiation versus entire SCL irradiation in 544 patients with clinical or pathological stage N2-3b breast cancer at our institution from January 2015 to December 2016. With a median follow-up time of 64.2 months, we found no significant differences in the cumulative incidence of SCL recurrence, disease-free survival, or overall survival between the two groups [17]. However, high-level evidence is lacking. The current SUCLANODE trial is a randomized trial investigating whether adding posterolateral SCL region to the medial SCL target volume will improve disease-free survival in patients with high-risk early breast cancer. Additionally, acute and late radiation-related toxicities and quality of life will be evaluated, with a particular focus on shoulder function and pain. The study protocol for the SUCLANODE trial is described in this article.

## Methods/design

### Study design

The SUCLANODE trial is an open label, multicenter, randomized, phase 3 trial comparing the efficacy and adverse events of medial SCL irradiation (M-SCLI group) versus entire SCL irradiation (E-SCLI group) in patients with high-risk early breast cancer after breast conserving-surgery or mastectomy. High-risk is defined as follows: pN2-3b disease if surgery was the initial treatment, or cIII or ypN1-3a/b if neoadjuvant systemic therapy was the initial therapy. The target sample size is 1650 participants. We hypothesize that E-SCLI, which includes the posterolateral SCL fossa in the SCL CTV, provide superior disease-free survival compared to M-SCLI group. The Flow chart of this trial is summarized in Fig. 1.

**Fig. 1 Fig1:**
[figure not shown]
Flow chart of the SUCLANODE trial. Abbreviations: BCS = breast conserving-surgery; ALND = axillary lymph node dissection; M-SCLI = medial supraclavicular lymph nodal irradiation; E-SCLI = entire supraclavicular lymph nodal irradiation; NAC = neoadjuvant chemotherapy; udALN = undissected axillary lymph node dissection; IMN = internal mammary node; SCL = supraclavicular lymph node

### Primary endpoint

The primary endpoint is disease-free survival (DFS), defined as the time from the date of randomization to the date of the first occurrence of any following events: ipsilateral invasive local recurrence (including ipsilateral breast tumor recurrence, ipsilateral chest wall recurrence), ipsilateral invasive regional recurrence (including axillary, supraclavicular, or internal mammary nodes), distant recurrence, contralateral invasive breast cancer, or death from any cause.

### Secondary endpoints

Overall survival: Defined as the time from randomization to death from any cause.SCL lymph node recurrence: Defined as the time from randomization to the date of the first ipsilateral supraclavicular lymph node recurrence.Local-regional recurrence: Defined as the time from randomization to the date of the first ipsilateral breast, chest wall, axillary, supraclavicular, or internal mammary nodal recurrence.Distance recurrence: Defined as the time from randomization to the date of the first distant breast cancer recurrence.Safety outcomes: The frequency and severity of acute and late radiation-related adverse events are assessed and graded based on the Common Terminology Criteria for Adverse Events (CTCAE) Version 4.0, or RTOG/the European Organization for Research and Treatment of Cancer (EORTC) late radiation morbidity scale and LENT-SOMA criteria if CTCAE grading not available.Patient-reported outcomes: Assessment of treatment-related symptoms, health-related quality of life via the EORTC Quality of Life Questionnaire (EORTC-QLQ-C30; version 3) and breast cancer module (QLQ-BR23), and upper limb function via the Quick Disabilities of the Arm, Shoulder and Hand (q-DASH) questionnaire.

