### Inclusion criteria

Female subjects aged 18 ~ 75 yeas on the day of signing informed consent.Histologically confirmed invasive breast cancer.Have undergone breast conserving-surgery or total mastectomy (including breast reconstruction) with negative margins and axillary lymph node dissection (≥ 10 lymph nodes dissected). Axillary level 3 dissection and internal mammary node dissection are not required but may be performed per surgeon’s discretion.Clinical or pathological stage: pathological N2-3b disease if surgery was the initial treatment; initial clinical stage III or pathological N1-3b if neoadjuvant systemic therapy was the initial therapy.Completion of neoadjuvant or adjuvant systemic treatment (taxane and/or anthracycline-based) consisting of at least 6 cycles.Will receive endocrine therapy for at least 5 years for estrogen receptor (ER) and/or progesterone receptor (PR) positive patients; will receive anti-HER2 (human epidermal growth factor receptor 2) therapy for 1 year for HER2 positive patients.Radiation therapy must begin no later than 12 weeks after the last breast cancer surgery or the last dose of adjuvant chemotherapy.Eastern Cooperative Oncology Group (ECOG) performance status of 0 or 1.Acquirement of informed consent.

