### Exclusion criteria

Clinical stage N3c at presentation (metastatic supraclavicular lymph node).Clinical stage T4 at presentation and failed to downstage after neoadjuvant systemic therapy.Stage IV (metastatic) breast cancer.ECOG performance status ≥ 2.History of any prior ipsilateral or contralateral breast cancer.Positive sentinel lymph node without further axillary lymph node dissection.History of prior radiation therapy.Current pregnancy and/or lactation.History of other malignancies except for appropriately treated skin basal cell carcinoma and cervical carcinoma in situ.Inability to tolerate chemotherapy, anti-HER2 therapy, or endocrine therapy.Current severe, uncontrolled systemic disease (e.g., clinically significant cardiovascular, pulmonary, hepatic, renal, hematologic, or psychiatric disease).Inability or unwillingness to comply with protocol requirements.

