The biophysical effects of radiotherapy are not tumor-specific and can also cause toxicity due to exposure of surrounding normal tissues. The toxicity is of particular concern in breast cancer as more patients become long-term survivors due to advances in systemic and local therapies. Expanding the SCL target volume will inevitably increase neck and shoulder radiation dose, potentially heightening acute and late normal tissue toxicity and reducing quality of life. Bazan et al. found 3D-CRT technique delivered significantly higher incidental dose to the shoulder and back versus IMRT technique, with a tend toward reduced q-DASH scores indicating less shoulder morbidity in patients treated with IMRT technique (*p* = 0.078) [20]. Our prior study also observed a significantly higher rate of pain in the E-SCLI group compared to M-SCLI (26.6% vs. 15.1%, *p* = 0.005) [17]. In this trial, we will evaluate shoulder function via q-DASH questionnaire, patients-reported shoulder/back symptoms, and quality of life. Additionally, a previous study showed 3D-CRT technique delivered significantly higher incidental radiation dose to the posterolateral SCL region than IMRT technique (46.7 Gy vs. 30.2 Gy *P* < 0.0001) when treating medial SCL region based on RTOG consensus [20]. We will utilize advanced IMRT, VMAT, or tomotherapy techniques instead of 3D-CRT technique to minimize incidental irradiation to the posterolateral SCL region in the M-SCLI arm.

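### Restricting the clinician-graded safety outcome to radiation-related events lets open-label attribution decide which late shoulder, neck and arm events count

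*Protocol article*

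**What the plan says.** The Secondary endpoints section of the protocol article defines the safety outcome in one sentence: "The frequency and severity of acute and late radiation-related adverse events are assessed and graded". CTCAE version 4.0 is the main scale, with RTOG/EORTC and LENT-SOMA criteria where CTCAE offers no grade.

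The setting for that definition is given elsewhere in the article:

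- **Blinding.** Study design: "The SUCLANODE trial is an open label, multicenter, randomized, phase 3 trial comparing the efficacy and adverse events".
- **Surgery.** Inclusion criteria require "axillary lymph node dissection (≥ 10 lymph nodes dissected"); Exclusion criteria remove "Positive sentinel lymph node without further axillary lymph node dissection".
- **Systemic therapy.** Inclusion criteria require at least 6 completed cycles in every patient. Patients with hormone-receptor-positive disease will also take endocrine therapy.
- **Safety focus.** Background says toxicity and quality of life will be evaluated "with a particular focus on shoulder function and pain".
- **Prior expectation.** Discussion: "Our prior study also observed a significantly higher rate of pain in the E-SCLI group compared to M-SCLI", with rates of 26.6% and 15.1%.

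**The concern.** An endpoint limited to radiation-related events invites a judgement of cause before an event is counted. That judgement comes after randomisation and is made by someone who may know whether the posterolateral region was treated. Dissection and systemic therapy can cause similar complaints, so the cause of a stiff or painful shoulder is often arguable. The investigators have also published an expectation about which arm will report more pain.

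Randomisation balances the underlying rate of such symptoms. It does not balance how they are classified afterwards. If the share of events attributed to radiation differs by arm, the clinician-graded comparison can show a difference that does not exist, or hide one that does. What is at stake is the credibility of the clinician-graded half of the safety comparison, above all for late shoulder, neck and arm events.

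**Working it through.** The article gives no figure for the safety outcome, so there is none to reproduce. The check has two parts.

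**1. How far does the wording expose each kind of event?**

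- *Acute events.* Follow-up names the acute toxicities by type, and neck and shoulder pain is among them. This leaves less room for attribution.
- *Late events.* Follow-up and Table 3 say when they are assessed (3 months after radiotherapy, then yearly) but print no list of types. Here the qualifier in the endpoint definition stands alone.
- *Baseline.* Table 3 marks both the acute and the late adverse-event rows at baseline, so change from baseline can be scored for both.
- *Patient-reported outcomes.* q-DASH, QLQ-C30 and QLQ-BR23 are a separate secondary endpoint. Table 3 schedules them at baseline, 3 months and yearly. No physician attribution enters them, although patients also know their arm.

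The exposed part is therefore mainly late shoulder, neck and arm events graded by clinicians.

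**2. What could unequal attribution do?** This is an illustration only.

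Inputs: n = 825 per arm (Sample size and statistical analysis). The true all-cause rate T, equal in both arms, and the attributed shares a_M (M-SCLI) and a_E (E-SCLI) are assumptions; the article gives none of them.

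Formulas: p_M = T × a_M and p_E = T × a_E; p̄ = (p_M + p_E)/2; SE = √[2 p̄(1 − p̄)/n]; z = (p_E − p_M)/SE; chance of two-sided p < 0.05 ≈ Φ(z − 1.96).

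- T = 25%, shares 60% and 70%: 15.0% against 17.5%; p̄ = 0.1625; SE = 0.0182; z = 1.38; Φ(−0.58) ≈ 28%.
- T = 25%, shares 60% and 80%: 15% against 20%; p̄ = 0.175; SE = 0.0187; z = 2.67; Φ(0.71) ≈ 76%.
- Equal shares: the nominal 5%.

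Range over other assumed true rates:

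| T in both arms | Shares 60% and 70% | Shares 60% and 80% |
|---|---|---|
| 20% | 12% vs 14%: 23% | 12% vs 16%: 65% |
| 30% | 18% vs 21%: 34% | 18% vs 24%: 85% |
| 40% | 24% vs 28%: 46% | 24% vs 32%: 95% |

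The distortion can also run the other way. Suppose true rates of 25% with E-SCLI and 20% with M-SCLI, and attributed shares of 60% and 75% (again assumed). Then 0.25 × 0.60 = 15% and 0.20 × 0.75 = 15%, and a real 5-point difference disappears.

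**The case against.** The strongest reply is that radiation-related names a class of event and is not a causality filter. The article describes no relatedness judgement. Follow-up gives acute toxicity as a list of types. Table 3 scores both acute and late radiation adverse events at baseline, when no event can have been caused by trial radiotherapy and prior radiotherapy is an exclusion. This is good evidence for the type reading, and it largely answers the concern for acute events. It does not settle late events, for which no types are printed and the endpoint sentence is all the reader has. If types are meant, saying so costs the sponsor nothing.

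Second, q-DASH and QLQ-BR23 cover shoulder and arm function without attribution. This stands. A reader might infer that the benefit-harm balance of the larger volume rests largely on the clinician-graded comparison; the article does not support that, because the patient-reported endpoints address the same harms. They limit the damage but do not repair the clinician-graded outcome.

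Third, the full protocol may contain a late-event list, an attribution rule or blinded assessors. That is possible, and their absence from an article is not the point made here. The point is the stated definition.

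Fourth, the illustration rests on assumed shares, and the statistical section specifies no safety test. Both are true. A reader might take 28% or 76% as this trial's false-positive rate; the documents do not support that.

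**Conclusion.** The point holds as a weakness in how a secondary endpoint is defined. On its plain wording, unblinded attribution can decide which late shoulder, neck and arm events enter the clinician-graded safety outcome, in a population where all patients have competing causes for them. Acute events are less exposed.

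The size is not known. With 825 per arm and true rates of 20% to 40%, a 10-point gap in attributed share would raise a nominal 5% error to about 23% to 46%, and a 20-point gap to about 65% to 95%. These figures assume that attribution differs by arm, that it does so in one direction, and that a two-sided 5% test is applied. Without such a gap the error stays at 5%.

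It would go too far to infer that a causality filter is known to operate in this trial: the article shows wording that permits one, and other text that points away from it. Disease-free survival and its analysis are unaffected.

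**What to change.** In Secondary endpoints, define the safety outcome as new or worsened events since baseline of pre-listed types, graded as now and counted whatever their attributed cause. Use the acute list already in Follow-up and add a late list covering neck, shoulder and arm events. Compare these by arm, and report investigator-attributed events as supportive only. Carry the same wording into Follow-up.

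The cost is a sentence in the endpoint definition, a printed late list and a case-report-form instruction; the baseline assessments are already scheduled. The downside is slight dilution: background events enter both arms and shrink a relative difference. Accrual is ongoing. If only attributed events have been recorded so far, earlier unattributed ones may not be recoverable; the article does not say which.

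The change removes bias from attribution. It does not make the counts fully comparable, because the same unblinded clinicians would still elicit symptoms, grade them and judge worsening.

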### Exploratory outcome

To explore whether radiotherapy resistance mechanisms can be identified through analysis of tumor and blood sample derivatives. Future exploratory research into factors that may influence efficacy and safety may be performed on the collected and stored tumor and blood samples. Efficacy outcomes considered for this analysis will include local-regional recurrence and DFS, as appropriate.

### Inclusion criteria

Female subjects aged 18 ~ 75 yeas on the day of signing informed consent.Histologically confirmed invasive breast cancer.Have undergone breast conserving-surgery or total mastectomy (including breast reconstruction) with negative margins and axillary lymph node dissection (≥ 10 lymph nodes dissected). Axillary level 3 dissection and internal mammary node dissection are not required but may be performed per surgeon’s discretion.Clinical or pathological stage: pathological N2-3b disease if surgery was the initial treatment; initial clinical stage III or pathological N1-3b if neoadjuvant systemic therapy was the initial therapy.Completion of neoadjuvant or adjuvant systemic treatment (taxane and/or anthracycline-based) consisting of at least 6 cycles.Will receive endocrine therapy for at least 5 years for estrogen receptor (ER) and/or progesterone receptor (PR) positive patients; will receive anti-HER2 (human epidermal growth factor receptor 2) therapy for 1 year for HER2 positive patients.Radiation therapy must begin no later than 12 weeks after the last breast cancer surgery or the last dose of adjuvant chemotherapy.Eastern Cooperative Oncology Group (ECOG) performance status of 0 or 1.Acquirement of informed consent.

### Exclusion criteria

Clinical stage N3c at presentation (metastatic supraclavicular lymph node).Clinical stage T4 at presentation and failed to downstage after neoadjuvant systemic therapy.Stage IV (metastatic) breast cancer.ECOG performance status ≥ 2.History of any prior ipsilateral or contralateral breast cancer.Positive sentinel lymph node without further axillary lymph node dissection.History of prior radiation therapy.Current pregnancy and/or lactation.History of other malignancies except for appropriately treated skin basal cell carcinoma and cervical carcinoma in situ.Inability to tolerate chemotherapy, anti-HER2 therapy, or endocrine therapy.Current severe, uncontrolled systemic disease (e.g., clinically significant cardiovascular, pulmonary, hepatic, renal, hematologic, or psychiatric disease).Inability or unwillingness to comply with protocol requirements.

